##### Cost analysis

The economic evaluation will be performed as a cost-minimisation analysis. In addition, a budget impact analysis of selective HPE will be performed from governmental, insurer and hospital provider perspectives.

#### Secondary outcomes

The incidence of different histopathological diagnoses following appendicectomy and cholecystectomy.Value of the intraoperative assessment (ie, inspection and palpation) performed by the surgeon for detection of appendiceal neoplasms or GBC.Incidence of specimens with a recognised appendiceal neoplasm or GBC.Incidence of specimens with an unrecognised appendiceal neoplasm or GBC.Indication for additional diagnostic or therapeutic procedures following histopathological diagnosis of appendiceal neoplasms or GBC and its clinical consequences, both in terms of benefit and harm.Incidence of appendiceal neoplasms and GBC requiring additional diagnostic or therapeutic procedures.Incidence of residual tumour and/or positive lymph nodes found in the re-resection specimen.Incidence of postoperative complications within 90 days after additional resection.Value of the intraoperative assessment (ie, inspection and palpation) performed by the surgeon for detection of aberrant findings other than appendiceal neoplasms and GBC.Appendiceal specimens: incidence of parasite infection, endometriosis, granulomatosis and other aberrant findings that would and would not have been sent for HPE.Gallbladder specimens: incidence of adenoma, biliary intra-epithelial neoplasm, cholesterol polyp, inflammatory/hyperplastic polyp, adenomyomatosis and other aberrant findings that would and would not have been sent for HPE.

### Group size calculation

Group size calculation is based on the number of appendices and gallbladders with a tumour with clinical consequences benefitting the patient that would have been missed in case of a selective policy. According to systematic reviews, the incidences of appendiceal neoplasms and GBC are 7 per 1000 and 4 per 1000 patients, respectively.^1 2^ Data regarding the ability of surgeons to recognise these abnormalities and the consequences of these neoplasms are insufficient. It is however estimated that less than 1 out of 1000 examined specimens will contain an appendiceal neoplasm or GBC with clinical consequences benefitting the patient that is not recognised by the surgeon during the macroscopic assessment. Selective HPE will be considered safe if this number does not increase to 3 per 1000 patients. To demonstrate non-inferiority of selective compared with routine HPE, a sample size of 4462 per cohort achieves a 84% power to detect a difference of 0.002 using a one-sided binomial test at a target significance level of 0.025, assuming a baseline and actual proportion of 0.001, and a non-inferiority limit of 0.00299. The actual significance level achieved by the Fisher's exact test is 0.021. These two cohorts (one for appendices, one for gallbladders) only include the specimens that would not have been sent for HPE in case of a selective policy. If the rate of HPE can be reduced to 20%, 5578 patients per cohort (4462/0.8) should initially be included.

### Data collection

The local study team of each participating hospital will be responsible for entering the prospectively collected data into an electronic case record form build with Castor EDC, which is ISO 27001 and NEN 7510 certified.^24^ Pre/intraoperative data will be processed after surgery, and complemented with the postoperative histopathological outcomes when the pathology report is available (±two weeks after surgery). Pre/postoperative data will be obtained from the electronic patient database and pathology reports. Intraoperative data will be obtained from the scoring form that will be filled in by the surgeon after examination of the specimen. In case a neoplasm is found during HPE, additional data about postoperative management, including details of additional diagnostic tests and/or treatment, postoperative morbidity and HPE of re-resection specimens, will be collected.

### Monitoring of the primary endpoint

The reliability and quality of the primary endpoint will be assured in three ways: (1) revision of all pathology reports, (2) source data verification by remote monitoring of all cases with a histopathological diagnosis of appendiceal neoplasm or GBC and (3) estimation of the incidence of appendiceal neoplasms and GBC in the group of eligible patients that were unintentionally not included.

#### Source data verification

Independent remote monitoring will be performed by a qualified monitor of the Clinical Research Unit of the Amsterdam UMC. Monitoring will be limited to all cases with a histopathological diagnosis of an appendiceal neoplasm or GBC. The quality assessment will focus on comparing entered data with source documents. Since no informed consent is obtained in this study, anonymised source documents of relevant patients will be supplied by the local study teams.

#### Estimation of the incidence of neoplasms in unintentionally not included patients

Since the macroscopic assessment of appendices and gallbladders is currently not routine practice, surgeons and residents might unintentionally forget to assess the specimen and fill in the scoring form. It is expected that the macroscopic assessment will not be performed in approximately 5%–10% of all eligible patients. In order to determine whether our patient cohort is representative for all patients undergoing an appendicectomy or cholecystectomy, the incidence of appendiceal neoplasms and GBC in the group of patients that were not included has to be determined. This will be done in collaboration with Pathologisch-Anatomisch Landelijk Geautomatiseerd Archief (PALGA), the Dutch nationwide network and registry of histopathology and cytopathology that contains pathology reports of all pathology laboratories in the Netherlands with complete coverage of reports since 1991.^25^ The PALGA database will be used to assess the number of patients in the participating centres that were unintentionally not included in the FANCY study. By means of comparing the total number of appendiceal neoplasms and GBC found in the PALGA database to the study database, we will be able to identify the number of patients that were not registered in the FANCY study. In collaboration with a staff member of PALGA, the individual pathology reports (without patient identifying information) of these patients will be checked for exclusion criteria. Consequently, the (estimated) incidence of appendiceal neoplasms and GBC in the group of unintentionally not included patients will be known.

### Cleaning and locking of the database

The database will be locked and exported for statistical analysis as soon as all data are entered, and all missing items are checked with the local study team. After locking, the database will be archived in a licensed repository.

### Predefined statistical analysis plan

#### General principles

The analyses will be performed after data entry is completed, monitoring and cleaning of the data have been performed and the statistical analysis plan is accepted for publication. For the primary analyses, all patients who underwent an appendicectomy for appendicitis or cholecystectomy for cholecystitis or gallstone disease will be included. All analyses described below will be performed using the latest version of SPSS statistics (IBM Corp) at the time of analysis.

#### Baseline characteristics

Baseline characteristics will be expressed as medians and IQR, or counts and percentages. Baseline characteristics will be presented as shown in table 2 (appendices) and table 3 (gallbladders).

**Table 2 T2:** Baseline characteristics (appendices)

	Total (n=)
Age, years	Median (IQR)
Sex, n (%)	
Female	n (% of ‘Total’)
Male	n (% of ‘Total’)
Preoperative imaging, n (%)	
Ultrasound	n (% of ‘Total’)
Ultrasound+CT	n (% of ‘Total’)
Ultrasound+MRI	n (% of ‘Total’)
Ultrasound+CT+MRI	n (% of ‘Total’)
CT	n (% of ‘Total’)
MRI	n (% of ‘Total’)
CT+MRI	n (% of ‘Total’)
No preoperative imaging	n (% of ‘Total’)
Hospital	
Academic hospital	n (% of ‘Total’)
Teaching hospital	n (% of ‘Total’)
Non-teaching hospital	n (% of ‘Total’)
Macroscopic assessment performed by	
Surgeon	n (% of ‘Total’)
Resident	n (% of ‘Total’)
Both	n (% of ‘Total’)

**Table 3 T3:** Baseline characteristics (gallbladders)

	Total (n=)
Age, years	Median (IQR)
Sex, n (%)	
Female	n (% of ‘Total’)
Male	n (% of ‘Total’)
Preoperative diagnosis, n (%)	
Cholecystitis	n (% of ‘Total’)
Symptomatic cholelithiasis	n (% of ‘Total’)
Preoperative imaging, n (%)	
Ultrasound	n (% of ‘Total’)
Ultrasound+CT	n (% of ‘Total’)
Ultrasound+MRI	n (% of ‘Total’)
Ultrasound+CT+MRI	n (% of ‘Total’)
CT	n (% of ‘Total’)
MRI	n (% of ‘Total’)
CT+MRI	n (% of ‘Total’)
Other	n (% of ‘Total’)
No preoperative imaging	n (% of ‘Total’)
Surgical setting	
Acute	n (% of ‘Total’)
Elective	n (% of ‘Total’)
Hospital	
Academic hospital	n (% of ‘Total’)
Teaching hospital	n (% of ‘Total’)
Non-teaching hospital	n (% of ‘Total’)
Macroscopic assessment performed by	
Surgeon	n (% of ‘Total’)
Resident	n (% of ‘Total’)
Both	n (% of ‘Total’)

#### Primary outcomes

##### Oncological safety

The number of patients with a histopathological diagnosis of an appendiceal neoplasm or GBC with clinical consequences benefitting the patient will be reported in absolute numbers and percentages, and as number per 1000 examined specimens for both strategies of HPE (routine and selective). The data will be presented as in figure 1 (appendices) and figure 2 (gallbladders). For analysis of the primary outcome, only the specimens that would not have been sent for HPE in case of a selective policy (ie, specimens without an indication for HPE according to the surgeon) will be analysed. A selective policy will be considered safe, if, following an exact test, the one-sided upper limit at a 97.5% CI of the proportion of missed malignancies falls below 3 per 1000 examined specimens. The influence of the assessor of the specimen (surgeon vs resident) and hospital (academic hospital vs teaching hospital vs non-teaching hospital) on the primary outcome will be assessed with Poisson regression.

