The FANCY study will be performed in 60 out of 74 Dutch hospitals, including academic (n=6), teaching (n=37) and non-teaching hospitals (n=17). Centres that have already implemented a selective HPE policy for gallbladder specimens may choose to either only participate in the appendix part of the FANCY study or to return to the routine policy for the duration of the study period. Hospitals will be allowed to start patient accrual after local approval has been obtained, and a site initiation visit has taken place, including a presentation of the study protocol and instructions for the macroscopic assessment of the specimens. Due to variation in completion of hospitals’ local approval procedures, it was decided to open study sites in phases. Every first day of a new month, a group of hospitals will start patient accrual. To avoid bias, all hospitals will include patients for a duration of 9 months, even if this means that the required sample size is exceeded.

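### The planned Poisson regression of missed neoplasms on assessor and hospital type would rest on about 4 to 7 events per cohort, so a finite hospital-type estimate will often not exist

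*Protocol article*

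**What the plan says.** In the protocol article, the Oncological safety part of the predefined statistical analysis plan restricts the primary outcome to "only the specimens that would not have been sent for HPE in case of a selective policy". Safety is decided by an exact upper confidence limit, which must lie below 3 per 1000. The same paragraph then adds a model for the influence of assessor (surgeon against resident) and of hospital type: "academic hospital vs teaching hospital vs non-teaching hospital) on the primary outcome will be assessed with Poisson regression". It does not say whether the two factors enter one model or two. The Outcomes section keeps appendices and gallbladders apart, so their events cannot be pooled.

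The Group size calculation expects that "less than 1 out of 1000 examined specimens will contain an appendiceal neoplasm or GBC" will go unrecognised with consequences that matter to the patient. It plans on this basis: "a sample size of 4462 per cohort achieves a 84% power to detect a difference of 0.002", "assuming a baseline and actual proportion of 0.001, and a non-inferiority limit of 0.00299". The inclusion target follows: "If the rate of HPE can be reduced to 20%, 5578 patients per cohort (4462/0.8) should initially be included". Study design describes 60 hospitals, "including academic (n=6), teaching (n=37) and non-teaching hospitals (n=17"). Current status of the study reports 6902 appendix and 8387 gallbladder patients, with 53 of the 60 hospitals finished. Tables 2 and 3 record the assessor at three levels: surgeon, resident and both.

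**The concern.** A Poisson regression estimates a log rate ratio for each non-reference level of a factor. If a level has no event, that log rate ratio has no finite maximum likelihood estimate, and a Wald interval or p-value reported for it carries no information. The outcome here is meant to be very rare, one hospital category holds a tenth of the sites, and the two cohorts are kept apart. Empty levels are therefore to be expected.

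At stake is the one formal analysis of whether the missed-case rate depends on who inspects the specimen and where. The results are intended to inform guideline revision. A divergent ratio, or a non-significant one taken as reassurance for residents or for a hospital type, would mislead.

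**Working it through.** **1. Reproduce the design.** The inputs are n = 4462, limit 0.00299, true rate 0.001 and one-sided level 0.025. The largest count c with P(X ≤ c | 4462, 0.00299) ≤ 0.025 is c = 6. The actual level is 0.0210 (stated 0.021). Power is P(X ≤ 6 | 4462, 0.001) = 0.836 (stated 84%). Inclusion: 4462/0.8 = 5577.5, rounded up to 5578 as stated. The design figures hold.

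**2. Events available to the regression.** Expected events = 0.001 × specimens without an indication for examination. The 80% not-sent share is the article's planning figure, applied here to the reported accrual.

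- Planned size: 4462 × 0.001 = 4.46
- Appendices: 0.8 × 6902 = 5522; × 0.001 = 5.52
- Gallbladders: 0.8 × 8387 = 6710; × 0.001 = 6.71

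Under the article's exact rule, safety can be declared with at most 6, 8 and 11 events respectively.

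**3. Hospital type.** The article gives site numbers, not specimen numbers. Assume volume follows sites: shares 6/60 = 0.100, 37/60 = 0.617, 17/60 = 0.283. With independent Poisson counts of mean μ × share,

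P(some type has no event) = 1 − Π[1 − exp(−μ × share)].

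At μ = 4.46 the zero probabilities are exp(−0.446) = 0.640, exp(−2.75) = 0.064 and exp(−1.26) = 0.283. The result is 1 − 0.360 × 0.936 × 0.718 = 0.758.

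| Expected events | No academic event | Some hospital type empty (10% academic) | Same, academic share 5% to 20% |
|---|---|---|---|
| 4.46 | 64% | 76% | 86% to 64% |
| 5.52 | 58% | 68% | 81% to 52% |
| 6.71 | 51% | 59% | 76% to 41% |

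In the last column the rest of the volume is split 37:17 between teaching and non-teaching hospitals.

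**4. Assessor alone.** With a 50:50 split, P(a level has no event) = 1 − [1 − exp(−μ/2)]², which is 20%, 12% and 7%. With a 30:70 split it is 30%, 21% and 14%. The estimate is therefore finite in 70% to 93% of cases. Its precision is poor: with events split evenly, SE(log rate ratio) = √(4/μ) = 0.95, 0.85 and 0.77. The 95% interval then extends by a factor exp(1.96 × SE) of about 6.4, 5.3 and 4.5 in each direction.

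**5. Both factors in one model.** Simulation (4000 tables per scenario, with a check for existence of the estimate) gave non-existence of about 78–79%, 69–72% and 61–62% at a 10% academic share and a resident share of 30% to 70%. Over academic shares of 5% to 20% the range is about 43% to 89%.

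**6. Sensitivity.** Scaling accrual by 60/53 for the unfinished hospitals gives about 6.3 and 7.6 events. The chance of an empty hospital type is then 62% and 53% at a 10% academic share, and 45% and 34% at 20%. At a true rate of 3 per 1000 (about 13 to 20 events) it is about 29% to 14% at a 10% share. The article expects a rate below 1 per 1000, which moves the figures the other way.

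**The case against.** Several points on the other side stand.

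- **The assessor effect.** A reader might infer that the regression as a whole will usually return nothing. The documents do not support that. The article does not say that both factors share one model, and the assessor contrast alone usually has a finite estimate. Non-existence concerns hospital type, or a joint model.
- **The event ceiling.** A reader might take six events as the most that is compatible with safety. That holds only at 4462 specimens. Accrual continued past the target by design, and the ceiling rises to 8 and 11 at 5522 and 6710 specimens.
- **Specimen shares.** Volume by hospital type is not in the article. At 6.7 events the chance of an empty hospital type falls to 48% and 41% if academic centres supply 15% or 20%, so more likely than not does not hold everywhere.
- **Other information.** Tables 7 and 8 list every neoplasm with its assessor and whether examination was thought indicated, so missed cases by assessor will be visible. They have no hospital column. The exploratory comparison by assessor and hospital type concerns the rate of specimens sent, which is a different outcome.
- **Inference method.** The article does not name Wald intervals. A likelihood-ratio test and a one-sided profile bound remain computable when a level is empty.

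A condensed article may also leave a sparse-data fallback to a fuller document. But it does name the model, and that model fits badly with the event count implied by the article's own planning figures. None of the objections makes the regression informative.

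**Conclusion.** The point holds in limited form. At the planning rate of 1 per 1000, the regression has about 4.5 to 6.7 events per cohort. If volume follows site numbers, some hospital type is empty with probability of about 76%, 68% and 59%; over academic shares of 5% to 20% the range is 41% to 86%. The assessor contrast is usually estimable, but uncertain by a factor of about 4.5 to 6.4 either way even in the best case. These figures rest on the 1 per 1000 rate, the 80% not-sent share and the assumed specimen shares.

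A reader might go further and infer that the safety conclusion is compromised. It is not: that decision uses only the exact limit, whose design figures reproduce, and no decision rule depends on the regression. This is a fault in a supporting analysis that should be corrected.

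**What to change.** Replace the Poisson regression of the primary outcome, in each cohort, with a table of missed cases, number of specimens without an indication, and exact (Clopper-Pearson) limits for each level of assessor (surgeon, resident, and the combined level that Tables 2 and 3 already record) and each hospital type. If a comparison is wanted, name a one-factor exact test. State that a non-significant result is not evidence of no influence.

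The table would show openly how little a small level can say. With 10% of 4462, about 446 academic specimens, and no missed case, the 97.5% upper limit is 1 − 0.025^(1/446) = 0.0082, or 8.2 per 1000, well above the limit of 3.

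The cost is a few lines of text and the loss of an adjusted rate ratio for the primary outcome. If a penalised model is preferred, it has to be reconciled with the statement under General principles that all analyses will be done in SPSS. Moving the regression to all unrecognised neoplasms is not proposed here, because the article gives no figure showing that this outcome would have enough events.

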**Figure 1 F1:**
[figure not shown]
Number of patients with an appendiceal neoplasm with clinical consequences benefitting the patient that would have been diagnosed (green box) and missed (red box) in case of a selective policy. The gray dotted line indicates the total number of patients benefitting from clinical consequences of an appendiceal neoplasm, that would have been diagnosed in case of a routine policy.

**Figure 2 F2:**
[figure not shown]
Number of patients with gallbladder cancer with clinical consequences benefitting the patient that would have been diagnosed (green box) and missed (red box) in case of a selective policy. The gray dotted line indicates the total number of patients benefitting from clinical consequences of gallbladder cancer, that would have been diagnosed in case of a routine policy.

##### Costs

###### Economic evaluation

Considering that—under the non-inferiority hypothesis—1 or 2 per 1000 patients at maximum will experience health consequences from routine HPE, and 3 to 4 per 1000 patients may experience transient harm following unnecessary additional treatment, differences in effectiveness between the routine and selective strategy can best be addressed qualitatively (eg, by case reports). Quantitatively, a cost analysis from a healthcare provider will be the main focus of research.

During the study, all specimens will be sent for HPE, so the selective policy will not be observed. The comparison between both strategies will therefore be done through decision tree analysis. Observed distributions of histopathological findings under the routine policy will be used to define chance nodes in the reference tree of the model. Alternatively, both the distribution of histopathological findings in specimens that would have been sent for HPE as the distribution of histopathological findings in specimens that would not have been sent for HPE in case of a selective policy will be used to define chance nodes in the other main model tree.

In addition to the initial HPE, costs of other resources (eg, additional treatment, additional HPE, hospital stay) will be assigned to each end node in the model. If costs were observed under routine examination, but the specimen would not have been sent for HPE in case of a selective policy, they will be ignored if related to unnecessary use of healthcare resources. However, if these costs were justified, and the specimen would not have been sent for HPE in case of a selective policy, it will be assumed that these costs would nevertheless be generated at a later stage during the disease course, and thus included in the decision tree. In addition, a scenario analysis will be run with a 50% surplus penalty of these costs to compensate for yet unobserved extra costs of delayed healthcare at a later disease stage. Unit costing of hospital resources will be based on the Erasmus University Rotterdam/National Healthcare Institute guideline for costing in healthcare research.^26^ If specific unit costs are lacking in the guideline, local bottom-up or top-down costing initiatives in participating hospitals (eg, Amsterdam UMC) will be used.

All probabilities at the chance nodes will be assumed beta-distributed. Multiple theoretical distributions will be assessed for fitting the (observed) distributions of healthcare costs at the end nodes of the decision tree. If theoretical fits seem insufficient, a uniform distribution will be defined for the (observed) cost data. Monte Carlo simulation will be applied based on 25 000 draws from each distribution of input parameters. It is expected that a time horizon for the cost analysis of 6 months is sufficient to reliably estimate the cost difference between routine and selective HPE. Separate models will be built for the analyses of appendices and gallbladders.

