**Methods and analysis:**

This is a Dutch multicentre prospective observational study, in which removed appendices and gallbladders will be systematically assessed by the operating surgeon for macroscopic abnormalities suspicious for malignant neoplasms. After visual inspection and digital palpation of the removed specimen, the operating surgeon will report whether macroscopic abnormalities suspicious for a malignant neoplasm are present, and if he or she believes additional microscopic examination by the pathologist is indicated. Regardless of the surgeon’s assessment, all specimens will be sent for histopathological examination. In this way, routine histopathological examination can be compared with a hypothetical situation in which specimens are routinely examined by surgeons and only sent to the pathologist on indication. The two main outcomes are oncological safety and potential cost savings of a selective policy. Oncological safety of selective histopathological examination will be assessed by calculating the number of patients in whom a histopathological diagnosis of an appendiceal neoplasm or gallbladder cancer with clinical consequences benefitting the patient would have been missed. A cost analysis will be performed to quantify the potential cost savings.

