#### Primary outcomes

##### Oncological safety

Oncological safety of selective HPE will be assessed by calculating the number of patients per 1000 examined appendices or gallbladders with the histopathological diagnosis of an appendiceal neoplasm or GBC with clinical consequences benefitting the patient that would have been missed. In case of an appendiceal neoplasm, the following consequences will be considered beneficial: (1) HPE of the re-resection specimen shows residual tumour and/or positive lymph nodes, (2) treatment with (adjuvant) systemic or local chemotherapy, radiotherapy, immunotherapy or stem cell transplantation and (3) palliative treatment for metastases detected during staging procedures. If an additional resection is performed following the diagnosis of an appendiceal neoplasm, and no residual tumour and/or positive lymph nodes are found during HPE, this is considered harmful due to the potential risks of surgery the patient is exposed to. For GBC, evidence on the prognostic impact of revisional surgery and adjuvant therapies is limited and inconclusive.^22^ For pragmatic reasons, it was decided that all cases of GBC requiring additional diagnostic or therapeutic procedures (ie, ≥T1 b GBC) will be considered beneficial.

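### The base-case cost rule cancels the care of missed neoplasms, and a single 50% surplus scenario does not show how far the saving is from reversing

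*Protocol article*

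**What the plan says.** The abstract of the protocol article gives cost equal billing with safety: "The two main outcomes are oncological safety and potential cost savings of a selective policy". Under Primary outcomes, Cost analysis, "The economic evaluation will be performed as a cost-minimisation analysis". The Economic evaluation part of the predefined analysis plan explains that the selective policy will not be observed, because every specimen goes to the pathologist, so the two policies are compared in a decision tree. Beyond the initial HPE, "costs of other resources (eg, additional treatment, additional HPE, hospital stay) will be assigned to each end node in the model".

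Two rules apply to costs seen in specimens that the surgeon would not have sent:

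- For the selective tree, "they will be ignored if related to unnecessary use of healthcare resources".
- If they were justified, "it will be assumed that these costs would nevertheless be generated at a later stage during the disease course, and thus included in the decision".

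The next sentence adds one sensitivity check: "a scenario analysis will be run with a 50% surplus penalty of these costs to compensate for yet unobserved extra costs of delayed healthcare". The article gives no reason for choosing 50% and no unit costs. It sets a 6-month horizon and 25 000 Monte Carlo draws.

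**The concern.** The extra cost of a late diagnosis cannot be seen in this design, so it has to be assumed. The base case sets it at zero. That fixes the direction of the expected difference before any data are collected, and the number of missed consequential neoplasms has no influence on it. Surgeons who miss every such neoplasm and surgeons who miss none would show the same HPE saving per unsent specimen.

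This matters for two reasons. Cost is a main outcome, and the article expects its results to change guidelines. Also, the Oncological safety part of Outcomes uses the expected savings as one argument for accepting more missed diagnoses than the colorectal screening programme does. A reader of the cost result will want to know whether late treatment of missed cases could consume the saving. The base case cannot answer that, and one scenario at a fixed surplus answers it at one point only.

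**Working it through.** **The plan's own figure.** The article states no cost figure. Its nearest figure is the sample size, which reproduces. With 4462 unsent specimens and a limit of 0.00299, the exact rule accepts up to 6 missed cases: P(X ≤ 6) = 0.0210 at 0.00299 and 0.836 at 0.001 (stated: 0.021 and 84%). 4462/0.8 = 5577.5, so 5578. The cost point does not rest on this, but it supplies two missed rates to work with.

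**Inputs.** From the article:

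- the two cost rules and the 50% surplus (Economic evaluation);
- 1 missed per 1000 as the planning rate (Group size calculation);
- 3 missed per 1000 as the safety limit (Oncological safety).

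Assumed: all costs.

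Notation:

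- w: share of specimens unsent
- c: HPE unit cost
- A: mean unnecessary care per unsent specimen (≥ 0)
- m: missed consequential cases per 1000 unsent
- J: justified care cost per missed case
- s: surplus on J under the selective policy
- K: mean care cost beyond HPE in sent specimens

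**Cost per specimen.**

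- Routine: c + w(A + mJ/1000) + (1 − w)K
- Selective: (1 − w)(c + K) + w(1 + s)mJ/1000
- Difference: w(c + A − s·mJ/1000)

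In the base case s = 0, and the difference is w(c + A). J and m have dropped out. Over 200 000 random sets of inputs, the base-case difference was never negative.

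**The 50% scenario.** Per 1000 unsent specimens the saving is 1000c + 1000A − 0.5mJ. With A = 0 it reverses when J/c > 1000/(0.5m):

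- m = 1: J/c > 2000
- m = 2: J/c > 1000
- m = 3: J/c > 667

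Avoided unnecessary care raises these thresholds. For example, assume c = EUR 100 and A = EUR 35 (3.5 per 1000 at an assumed EUR 10 000 each). At m = 3 the reversing J is 135/0.0015 = EUR 90 000, against 100/0.0015 = EUR 66 667 with A = 0.

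**Break-even surplus.** Setting the difference to zero gives s* = 1000(c + A)/(mJ). With A = 0 this is 1000/(m·J/c). The last two columns give the simulated probability that the 50% scenario shows a saving, with the missed count drawn from Bin(4462, m/1000).

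| Assumed J/c | s* at m = 1 | s* at m = 3 | P(saving), m = 1 | P(saving), m = 3 |
|---|---|---|---|---|
| 100 | 1000% | 333% | 1.000 | 1.000 |
| 200 | 500% | 167% | 1.000 | 1.000 |
| 400 | 250% | 83% | 1.000 | 0.990 |
| 800 | 125% | 42% | 0.998 | 0.314 |

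At the upper left the saving would survive a surplus of 1000%, twenty times the planned one. At the lower right it fails below the planned one. When the 50% scenario shows a saving, it does not say whether the break-even surplus is 83% or 1000%.

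**The case against.** A reader might infer that the cost outcome can never come out against selective HPE, whatever the data. The documents do not support that:

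- The sentence directly after the rule prespecifies the 50% surplus, and that scenario can reverse the sign (the 0.314 in the table).
- If no specimen is withheld, the difference is zero.
- The list of cost items is open. It does not name the surgeon's assessment but does not exclude it. With 80% unsent, A = 0 and an assumed HPE cost of EUR 50 to 150, an assessment cost of EUR 40 to 120 per specimen would remove the saving.
- The article does not say how draws in the two trees are paired. With independent draws, up to 2.7% of simulations were negative under assumed inputs, although the mean stayed positive.

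A reader might also infer that the saving is only the number unsent times the HPE price. That does not hold either. For appendices, a re-resection without residual tumour or positive nodes is classed as harmful, so unnecessary care is a real term that depends on the data. For gallbladders the article says that "all cases of GBC requiring additional diagnostic or therapeutic procedures (ie, ≥T1 b GBC) will be considered beneficial". If justified care follows that label, which the Economic evaluation does not state, this care cancels. Care after T1a cancer or a benign neoplasm lies outside the label and may still be unnecessary.

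Three broader objections carry weight:

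- The stated aim is to quantify savings, with no test or threshold for cost, so a base case that informs only on size is still useful.
- Missed cases are judged separately by the safety outcome.
- Charging missed cases in full, although their care might fall after the 6-month horizon, leans against selective HPE.

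These points limit the criticism. They do not supply the missing information, which is how much extra cost of delay the saving can absorb.

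**Conclusion.** The base-case rule is workable, but it settles the direction of the expected difference by assumption. On the listed cost items, the saving per unsent specimen is c + A, which is never negative and is unaffected by the number of missed consequential neoplasms. Whether missed cases could offset the saving rests on one surplus value with no stated rationale. Over assumed cost ratios of 100 to 800, with no unnecessary care avoided, the break-even surplus runs from 1000% to 125% at 1 missed per 1000 unsent and from 333% to 42% at 3 per 1000. Real unit costs would narrow this range, but the article gives none. This should be improved before the cost analysis is run. It does not invalidate the cost outcome, and it does not touch the safety rule.

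**What to change.** In the Economic evaluation part:

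1. Keep the base case and label it as the saving assuming that delay adds no cost.
2. Extend the 50% scenario to a threshold analysis in each of the two models. Vary the surplus on the justified costs of missed cases from 0% upwards and keep 50% as one point.
3. Report the break-even surplus with its interval from the same 25 000 draws, at the observed missed rate and at the upper confidence limit that the safety analysis already produces. With 6 missed of 4462, for example, that limit is 2.92 per 1000.
4. Show HPE avoided and unnecessary care avoided as separate lines.
5. State the break-even value beside any claim of savings.

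The cost is some wording and a loop over one parameter in the planned simulation; no new data are needed. The article places the analyses after acceptance of the plan, so on its own timetable the change could be prespecified. The drawback is slightly more analysis and a savings statement that becomes conditional.
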